### Data collection

After the intubation is complete the personnel involved complete a data sheet included in the trial enrollment pack. Data recorded includes patient demographics, procedural details, procedural and post-intubation complications encountered.

*Patient demographic details*; age, date & time of intubation and medical record number (for 28 day follow-up).

*Procedural details*; location of intubation (ED or pre-hospital), lowest pre-intubation GCS, intubation drugs used, experience of intubation operator, evidence and nature of macroscopic aspirate seen and grade of laryngoscopic view obtained.

*Procedural complications*; 3 or more attempts to place the ETT in the trachea, > 10 minutes using conventional laryngoscopy, required change of operator, termination of the attempt at RSI, use of laryngeal mask or surgical airway.

*Post-intubation complications encountered within 30 minutes of RSI*; severe hypotension (Systolic blood pressure < 60 mmHg), severe hypoxaemia (SaO_2 _< 70%), death and cardiac arrest.

The data sheet and SD card containing weight data will be sent to the Trial Coordinator who will enter the data into a password-protected database. Each episode of RSI has a unique randomly assigned number within the database (Plate Number). This number will be linked to the episode of service, and the pepsin assay result will be automatically appended to the corresponding patient data set in the database. The investigators are therefore blinded to the results coming in from the laboratory.

At 28 days the patient notes will be reviewed. The acute physiology and chronic health evaluation (APACHE II) score and diagnostic code will be determined and any treatment for aspiration as an inpatient (discharge diagnosis of aspiration pneumonitis/pneumonia or antibiotic therapy explicitly instituted to treat for aspiration pneumonia) will be noted.

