## Background

Rapid sequence intubation (RSI) is the process by which anaesthetic and neuromuscular blocking agents are administered in rapid succession to facilitate endotracheal intubation [1]. In the emergency department (ED) RSI is typically performed on acutely ill or injured patients who are often not fasted, increasing the risk of gastric aspiration during the process. In 1961 Sellick reported using "occlusion of the upper oesophagus by backwards pressure on the cricoid ring against the bodies of the cervical vertebrae to prevent gastric contents from reaching the pharynx" during induction of anaesthesia in patients at high risk of aspiration [2]. Cricoid pressure (CP) was subsequently adopted as an integral component of RSI in EDs despite inadequate scientific evaluation of its risks and benefits; its effectiveness has subsequently only been demonstrated in cadavers [3-6]. No randomised controlled trials have shown any benefit of its use during RSI. Furthermore the application of CP may be associated with increased risks to the patient: impeding airway management [7,8]; prolonging intubation time by obscuring laryngeal view [9,10]; inducing nausea/vomiting [10] and oesophageal rupture with excessive force [11]. Paradoxically, CP may indeed promote aspiration by relaxing the lower part of the oesophagus [12]. Some case reports note that tracheal intubation was impeded by CP [13] and regurgitation occurred despite application of CP [14,15], possibly due to its improper application.

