Aspiration of gastric or oropharyngeal contents into the larynx and lower respiratory tract may lead to various pulmonary syndromes, most notably pneumonia and pneumonitis. The true incidence and clinical significance of aspiration during RSI is difficult to establish due to the heterogeneous nature of pathologic processes of critically ill patients requiring an emergency airway. Compounding this is the fact that many patients aspirate prior to intubation or arrival at ED and that repeated attempts at intubation increased the incidence of aspiration (Mort et al. 2004). Mort reported that the rate of aspiration increased from 1.9% with one attempt at intubation to 22% with three or more attempts [36]. Given these limitations, the incidence of aspiration appears to lie anywhere between 0.8% [36] and 22% [37]. There is currently no widely available test to determine whether pulmonary aspiration has occurred during RSI. Pepsin detection has been described as a potential aspiration biomarker [38] since it is uniquely secreted in stomach. Ufberg has developed and validated a specific and sensitive pepsin assay as a marker of aspiration [39]. Using the assay he found pepsin in the lungs in 50% of patients intubated in the pre-hospital setting, and 22% of patients undergoing RSI in the ED [37], however there was no longitudinal follow-up to see whether the presence of pepsin in the lungs was linked to subsequent development of aspiration syndromes. It was also not possible to determine if aspiration occurred prior to or at the time of intubation.

The value of CP in RSI is under increasing scrutiny [40,41]. Since its introduction in the 1960s anaesthesia practices and airway management techniques have improved leading some to wonder what contribution CP now makes towards reduced aspiration rates [40]. Critically ill patients presenting to the ED are also likely to have aspirated prior to intubation [40], therefore negating necessity for CP in the ED.

Emergency physicians today need evidence to support the use of CP in the ED. The current study aims to address these issues, being designed to evaluate the effectiveness, safety and need for CP during RSI in EDs.

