### Study objectives

#### Primary aims

• Test the hypothesis that the use of CP during RSI in the ED does not prevent aspiration.

• Investigate the effect of CP on RSI and associated incidence of difficulty or failed intubation.

• Determine the incidence of pre-hospital aspiration.

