#### Secondary outcome measures

• Grade of laryngeal view

• Detection of pepsin in oropharyngeal aspirates

• Procedural complications associated with intubation

• Immediate complications (associated with RSI) within 30 minutes of intubation

• Lowest pre-intubation GCS

• Survival to 28 days/hospital discharge

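### Number of attempts and duration of intubation are listed only as yes/no events at high cut-offs, so a second attempt or a moderate prolongation is not distinguished

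*Protocol article*

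**What the plan says.** The second of the Primary aims is to "Investigate the effect of CP on RSI and associated incidence of difficulty or failed intubation". The Background gives the reasons: among the possible harms of cricoid pressure it lists "impeding airway management" and "prolonging intubation time by obscuring laryngeal view". It also cites a report that "the rate of aspiration increased from 1.9% with one attempt at intubation to 22% with three or more attempts".

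Under Data collection, the procedural complications begin with "3 or more attempts to place the ETT in the trachea, > 10 minutes using conventional laryngoscopy" and continue with "required change of operator, termination of the attempt at RSI, use of laryngeal mask or surgical airway". The procedural details include the "grade of laryngoscopic view obtained", and "Grade of laryngeal view" is a secondary outcome. Neither a count of attempts nor an elapsed time appears in Data collection or among the primary and secondary outcome measures. The only clock item listed is the date and time of the intubation.

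The Analysis section provides chi-squared or Fisher tests for proportions, the t test for means, and Mann-Whitney for ordinal and continuous variables.

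**The concern.** Attempts and time are naturally a count and a continuous measure. Cutting each at a high value discards everything below the cut. A shift from one attempt to two, or from two minutes to three, leaves both items unchanged.

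This matters in two ways. First, if the visible-scale arm made intubation somewhat slower or less often successful at the first pass, these two items would produce few extra events. A finding of no difference on them would then be hard to tell apart from a lack of resolution. Second, the protocol itself links attempt number to aspiration, the primary outcome. Without the count, that link cannot be described across one, two, and three or more attempts.

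**Working it through.** **1. The plan's own figure.** From Sample size: 11% against 0%, 90% power, alpha 0.05. Two-sided, pooled-variance formula:

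n = [1.960·√(2·0.055·0.945) + 1.282·√(0.11·0.89)]² / 0.11² = 88.2

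With continuity correction: (88.2/4)·[1 + √(1 + 4/(88.2·0.11))]² = 105.6, so 106 per arm. The stated figure reproduces. It concerns aspiration only; no calculation is given for difficulty of intubation.

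**2. Inputs for the illustration.** n = 106 per arm is from the protocol. Everything else here is assumed, because the documents give no distribution of intubation time and no rate for either cut-off: log-normal times, control median 2 minutes, log-SD 0.8, two-sided 5%.

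**3. The 10-minute cut-off.** The proportion above 10 minutes is 1 − Φ([ln(10/2) − ln r]/SD), where r is the ratio of times between arms. Power is Φ[(d − 1.96·se0)/se1], with se0 the pooled and se1 the unpooled standard error.
- Control: 1.609/0.8 = 2.01, giving 2.2%.
- r = 1.5: (1.609 − 0.405)/0.8 = 1.50, giving 6.6%. Power = Φ[(0.0440 − 1.96·0.0282)/0.0281] = Φ(−0.40) = 34%.
- r = 1.25: (1.609 − 0.223)/0.8 = 1.73, giving 4.2%. Power = Φ[(0.0194 − 1.96·0.0241)/0.0241] = Φ(−1.16) = 12%.

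**4. Recorded time.** t test on log time, 210 degrees of freedom, non-centrality (ln r/SD)·√(106/2).
- r = 1.5: 0.507 × 7.28 = 3.69, power 96%.
- r = 1.25: 0.279 × 7.28 = 2.03, power 52%.

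**5. Range over the assumed spread** (same formulas; cut-off v recorded time):

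| log-SD | times 50% longer | times 25% longer |
|---|---|---|
| 0.6 | 22% v >99% | 9% v 77% |
| 0.8 | 34% v 96% | 12% v 52% |
| 1.0 | 35% v 84% | 13% v 37% |

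Using the tests named in the Analysis section at log-SD 0.8 and r = 1.5, exact Fisher power for the cut-off is about 22%, and simulated Mann-Whitney power for recorded time is about 95%.

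**6. Attempts.** Assume a shift from 80/15/5% (one / two / three or more) to 65/27/8%.
- Three or more, 5% v 8%: Φ[(0.03 − 1.96·0.0339)/0.0338] = Φ(−1.08) = 14%.
- More than one, 20% v 35%: Φ[(0.15 − 1.96·0.0613)/0.0605] = Φ(0.49) = 69%.

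**7. Dependence on how common the threshold event is.** Power to detect a doubling at 106 per arm (normal approximation / exact Fisher): 2% to 4%, 13% / 5%; 5% to 10%, 28% / 20%; 10% to 20%, 53% / 46%; 20% to 40%, 89% / 87%. The cut-offs are a weak basis for comparison if the events are uncommon and an adequate one if they are not. The documents do not say which.

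**The case against.** A reader might infer that the trial can see only the rarest difficult intubations. The documents do not support that. The same list records change of operator, abandonment of the RSI attempt, laryngeal mask and surgical airway, any of which can occur without a third attempt or ten minutes. Laryngeal view is graded, is a secondary outcome, and can be compared by Mann-Whitney. It measures the very route by which the Background says intubation is prolonged. No rates are given, so calling the cut-off events rare is an assumption. This stands, and it limits the point to attempts and time. Grade of view captures the mechanism and not the resulting delay, and the other items are mostly rescue or failure events.

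A reader might also infer that duration is irrecoverably lost. In both arms the operator stands on logged scales sampled 60 times a second, and force is held until tube placement is confirmed and the cuff inflated. That allows partial recovery. The trace marks neither the first laryngoscopy nor separate attempts, and force is applied only as required and may be changed on instruction, so it is only a rough proxy.

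Nor are repeated attempts named as a risk of cricoid pressure. The Background ties them to aspiration, and the cut-off of three matches the upper category it cites.

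An incidence of difficult intubation does need a yes/no definition, and the listed complications supply one. That is fair, but the definition can be derived from a count and a time, whereas the reverse is impossible. The data sheet itself is not shown and may hold more than the article lists.

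Finally, both arms receive cricoid pressure, and nothing in the documents supports a contrast as large as 50% longer times. That stands, and is why the 25% case is shown beside it.

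**Conclusion.** The point holds in limited form, as an inexpensive improvement and not as an error that undermines the trial. As listed, a second attempt and any prolongation short of ten minutes are not distinguished by the two items meant to register them, although the protocol's own aims and rationale make both of interest. Other aspects of difficulty are captured.

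The direction of the loss is the same in every scenario tried. Its size is illustrative: at log-SD 0.8, about 34% against 96% power if times are 50% longer, and about 12% against 52% if 25% longer. These figures rest on an assumed log-normal distribution with a 2-minute median, and they test each cut-off alone, without the other complications or the graded view. At the smaller effect, recorded time would itself be underpowered.

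**What to change.** On the data sheet, replace the two threshold items with two numeric fields: the number of attempts, and the time from first laryngoscopy to end-tidal CO2 confirmation. The latter end point is already an event in both arms' procedures. Compare first-pass success by chi-squared or Fisher and intubation time by Mann-Whitney, both already in the Analysis section. Derive the three-attempt and ten-minute categories from these fields, so that nothing now planned is lost. Use the scale log as a check on the recorded duration.

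The cost is two numeric fields in place of two tick-boxes. The real downside is that someone must note two times during an emergency; the scale log backs this up only in part.

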Ostensibly a simple procedure, CP is in practice a complex manoeuvre which is difficult to perform optimally [12]. The amount of force used by the cricoid operator is a crucial factor in proper application of CP. A force in the range of 30 - 40 Newtons (N) applied to the cricoid ring is generally accepted as sufficient to occlude the oesophagus [5,12,16-18], preventing regurgitation of gastric contents. Studies have revealed that the knowledge of cricoid force theory and concept of the forces required is poor amongst both anaesthetic and ED staff [19-31]. Considerable ranges in the amount of force used by staff when applying force to cricoid models have been described [29,31,32]. Furthermore, when ED staff were asked to apply "ideal" CP to a human larynx model, only 25% of the group reached the target range, while 47% applied insufficient and 28% applied excessive force [29]. At forces greater than 44 N the patient is considered to be at risk of oesophageal rupture [5,10]. Training staff how to gauge the correct amount of force to use is effective in the short term only, however, in practice training is rarely undertaken [23,25,26,31,33,34]. In addition, the effect of fatigue on the ability of the cricoid operator to maintain CP within the target range for the duration of prolonged intubations has been questioned [35]. The use of floor scales to provide a means of gauging the amount of force applied to a cricoid model has been demonstrated [25], however its use in real-time measurement during RSI has not been reported.

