## Discussion

The primary aim of this study is two-fold. Firstly, by comparing the incidence of aspiration of pepsin in the intervention and control groups and prospectively documenting the benefits and adverse events associated with 30 - 40 N of cricoid force during RSI, it aims to challenge the notion that CP prevents aspiration. Secondly, since the presence of pepsin in the oropharynx will be indicative of aspiration having occurred prior to intubation by virtue of the injury sustained by the patient, determining the incidence of pre-intubation aspiration will allow us to further evaluate the relevance of CP in the RSI algorithm in ED.

The secondary aim of this study is also two-fold. Firstly, defining any observed correlation between aspiration and pre-intubation Glasgow coma score will provide evidence for indications for the use of CP dependent upon the level of patient consciousness. Secondly, a correlation between detection of pepsin in trachea and development of aspiration syndromes will support the use of Fibrinogen plate assay in a clinical setting for their early detection and treatment.

It is conceivable that this research could also give rise to novel therapy. For example, once the incidence of serious aspiration and a pepsin positive assay is identified, the plate assay for pepsin could potentially be performed at the bedside, enabling doctors to treat aspiration pneumonia much earlier. It may also lead to amendments to the algorithm for RSI if CP is found to be deleterious.

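### Nausea/vomiting and oesophageal rupture, two harms the protocol attributes to cricoid pressure, have no data item, so its adverse-event aim is only partly covered

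*Protocol article*

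**What the plan says.** **What is promised.** The Background of the protocol article ends by describing the study as "being designed to evaluate the effectiveness, safety and need for CP during RSI in EDs". The Discussion includes in the primary aim "prospectively documenting the benefits and adverse events associated with 30 - 40 N of cricoid force during RSI". Under Primary aims, the item closest to safety is narrower: "Investigate the effect of CP on RSI and associated incidence of difficulty or failed intubation".

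**Which harms are named.** The Background lists "impeding airway management", "prolonging intubation time by obscuring laryngeal view", and "inducing nausea/vomiting [10] and oesophageal rupture with excessive force [11". It adds that cricoid pressure may itself promote aspiration. On force it says: "At forces greater than 44 N the patient is considered to be at risk of oesophageal rupture [5,10".

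**What is collected.** Data collection itemises:
- airway difficulty: three or more attempts, more than 10 minutes of conventional laryngoscopy, change of operator, abandoned attempt, laryngeal mask or surgical airway;
- grade of laryngoscopic view, and any macroscopic aspirate seen;
- "Post-intubation complications encountered within 30 minutes of RSI": systolic pressure below 60 mmHg, oxygen saturation below 70%, death, cardiac arrest;
- at the 28-day notes review: APACHE II score, diagnostic code and treatment for aspiration.

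Outcome measures adds pepsin in tracheal and oropharyngeal aspirates, and survival to 28 days or discharge.

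**The concern.** The article says it will document the adverse events of cricoid force, yet two of the harms it gives as reasons for doubting the manoeuvre have no place to be written down. If the listed items are what is collected, a report would be silent on vomiting under cricoid force and on oesophageal injury. A reader could take that silence as absence of harm, although nobody was asked to look. The Discussion says the intubation algorithm may be amended if cricoid pressure proves deleterious, so what the trial can say about harm bears on how its result is used.

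**Working it through.** **1. Named harms set against recorded items.**

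| Harm named in Background | Where it is measured | Covered? |
|---|---|---|
| Impeded airway management | Procedural complications (Data collection) | Yes |
| Longer intubation, obscured view | Grade of view; flag for more than 10 minutes | Yes |
| Promotion of aspiration | Primary outcome | Yes |
| Nausea/vomiting | No item | No |
| Oesophageal rupture | No item | No |

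Three of five are covered.

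**2. Do other items stand in for the missing two?**
- *Macroscopic aspirate.* No timing is stated, so contents regurgitated under cricoid force cannot be told from earlier soiling. The Background says many patients aspirate before intubation or arrival.
- *Oropharyngeal pepsin.* Aspirate collection takes the sample after the tube is placed, but the Discussion reads a positive result as aspiration before intubation. Regurgitation provoked by cricoid pressure would be counted as a pre-intubation event.
- *Diagnostic code.* It might show a coded rupture but is not defined as a harm outcome.
- *Logged force* (60 readings per second). This identifies exposure above 44 N, but not its consequence.

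**3. The plan's sample size.** Inputs from Sample size: 11% versus 0%, power 90%, alpha 0.05, 106 per arm. Sidedness is not stated; two-sided is assumed. With mean rate 0.055 and difference d = 0.11:

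n0 = [1.960 × √(2 × 0.055 × 0.945) + 1.282 × √(0.11 × 0.89)]² / 0.11² = 88.2

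With continuity correction: n = (n0/4) × [1 + √(1 + 4/(n0 × d))]² = (88.2/4) × [1 + √(1 + 4/9.70)]² = 105.6, so 106. The stated figure is reproduced. Adding form items does not change it.

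**4. What that sample can say about injury.** With zero events in n patients, the one-sided 95% upper limit is 1 − 0.05^(1/n):
- n = 106: 2.8%
- n = 212: 1.4%

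The documents give no rupture rate. The chance of at least one event in 212 patients is 1 − (1 − p)^212. At assumed rates of 0.01%, 0.1% and 1% it is 2.1%, 19.1% and 88.1%.

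**5. What it can say about vomiting.** The documents give no rate here either. At 106 per arm (two-sided 0.05), power for assumed rates of 5% versus 10%, 15% and 20% is 28%, 68% and 92%. Only a large difference would be detected reliably.

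**The case against.** The strongest reply is that the article defines its safety question narrowly. The Discussion paragraph of the Abstract frames benefit and risk as aspiration and difficult or failed intubation, and Primary aims does much the same. Both can be answered from the recorded data. The wider promises sit in general sentences of the Background and Discussion. A journal article is also condensed: the data sheet introduces its contents as what the data include, and the summary of the 28-day review is evidently incomplete, since survival is an outcome but is missing from it.

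Much of this stands, and it rules out several stronger readings that a reader might infer:
- *That the safety objective cannot be answered.* Three of the five named harms are measured, including the one in the listed aim.
- *That a 30-minute window limits all safety data.* It governs one list only. Procedural complications, the notes review and survival lie outside it.
- *That laryngeal or cricoid injury is also a named harm left out.* The Background does not name either.
- *That about 30 control patients (0.28 × 106 = 29.7) would be exposed to dangerous force.* The 28% comes from staff pressing a larynx model. It means above the target range, not above 44 N, and trial staff receive mandatory training.

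The reply does not dispose of the point. The complication categories are spelled out item by item, several with cut-offs, and give content to the two complication outcomes. The Discussion makes documenting adverse events part of the primary aim. Set against that aim, two harms the article itself names are absent, and the proxies do not replace them.

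**Conclusion.** The point holds in a limited form. Two of the five harms that the Background attributes to cricoid pressure have no defined item, so the adverse-event aim is partly, not wholly, covered. This assumes that the itemised lists in the article reflect the data sheet and notes review; if the full protocol already carries these items, only the article needs correcting.

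The gain from closing the gap is modest. An injury item would document cases but would not support a comparison between arms: zero events would leave rates up to about 2.8% per arm, or 1.4% overall, compatible with the data (one-sided 95%). A vomiting item could support a comparison only if the difference were large. No passage plans to claim safety from an absence of events, so misreading is a risk to guard against, not an error already in the plan. This is a cheap improvement.

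**What to change.** - On the intubation data sheet, add one yes/no item: vomiting or regurgitation seen while cricoid force was being applied.
- In the 28-day notes review, add one item: any oesophageal injury documented during the admission.
- List both under Secondary outcome measures as safety outcomes, reported by arm.
- Report injury as counts with the upper confidence limit, stating whether it is one- or two-sided, and say that the trial is not sized to compare injury between arms.
- Leave the 30-minute list as it is.

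The cost is two extra items on forms already completed, with no new test, visit or patients. The limitation is that only clinically recognised events will be found, so the injury estimate stays imprecise.
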